## Introduction

Early childhood development is fundamental for a sustainable future for all [1-4]. It is crucial to educate parents and caregivers about the importance of early childhood and the domino effect it has on the future [5-7]. Children have an extraordinary capacity to learn, understand, and feel, even without acquiring language and communication skills. The first 1,000 days of life are crucial to the growth and early brain development [8-11]. Neuroplasticity is at its peak with an astounding 1,000 neuronal connections being made per second [12]. As children explore and interact with their surroundings, new synaptic connections are formed, which are further reinforced by positive experiences. Early childhood is a critical period for physical, emotional, and cognitive development, as well as a predictor of future development and skill acquisition. As neuroplasticity declines after the early years, it becomes increasingly hard to offset the effects of toxic stress, neglect, and poor parenting in the future [12]. Today, 250 million children from middle- and low-income countries are unable to reach their development potential [13]. While research has shown that a multitude of interlinking environmental factors, such as immunological, physiological, epigenetic, and psychological factors, influence brain development in a child, a key intervention provided through responsive caregiving can offset the detrimental effects to a significant extent [14]. Hence, parental intervention in this critical time is crucial, as backed by evidence. An early childhood development intervention was introduced in Jamaica for stunted children from low-income families. Children who had received psychosocial stimulation during this period had a 25% increase in earnings and future outcomes [15]. The impact of timely intervention cannot be understated.

Responsive caregiving during the early years lays the foundation for early childhood development and acquisition of essential skills in the future. Responsive and nurturing care provided by primary caregivers can foster brain development, allowing a child to feel a sense of security and safety, build a strong parent-child connection, and strengthen emotional and cognitive growth. A child who has been brought up in a nurturing and responsive environment can easily adapt to the adversity and stresses of life in the future. The importance of responsive parenting in early childhood is emphasized and reiterated by research. A study revealed that preschool children who were provided with responsive caregiving had higher hippocampal volumes. The increase in hippocampal volume is not only indicative of optimal childhood development but also reflects enhanced stress reactivity [16]. Positive experiences provided through nurturing create a virtuous cycle of health, love, and security in children and shape their brains from an early age. According to the life course theory, the early years of life are most sensitive to intervention [17]. The introduction of programs that target caregivers and parents can have a transformative impact on early childhood development. The key to a successful parenting program is educating caretakers about the importance of nurturing care and the far-reaching effects it has on child development. A nurturing environment is sensitive to a child’s needs, provides security and protection, allows for stimulation through play and learning opportunities, and ensures adequate nutrition status and well-being of a child [18]. Research has shown that maternal nurturing care can go as far as attenuating the adverse effects of childhood poverty and adversity [19,20]. Thus, it is important to recognize the power that parenting education interventions can hold.

The UN’s inclusion of early childhood development in the Sustainable Development Goals has resulted in a greater focus on child wellbeing and the introduction of policies and strategies that support this aim [21]. One such intervention that has shown promise is the introduction of parenting programs.

A program that will significantly impact childhood development needs to be multi-sectoral and holistic. While information dissemination through education is essential, teaching parents, especially those who are first-time parents, techniques and strategies to provide childcare is as important. Children thrive with positive attention and focus. Parenting interventions that were initiated in Brazil and Bangladesh had a two-pronged approach with a mix of group and home visits. Both programs showed positive results with enhanced future outcomes, in terms of psychosocial factors and competency [22]. Parenting programs that focus on child enrichment and learning, positive parent-child interactions, and stimulation opportunities for children have the potential to significantly impact development. Practice plays and strategies to provide emotional support to children, as well as caregiving routines, can be taught through these interventions. Moreover, longitudinal follow-ups of parental programs have shown a wide range of beneficial effects and much promise. In children exposed to poverty, the implementation of these programs showed improved health biomarkers [23], intelligence quotients [24], and adult earnings.

In this research, we intend to implement and adapt the model of newborn responsive parenting education in the primary care settings of remote Pakistan and Afghanistan, which we have already implemented in a tertiary care setting [25,26]. This protocol is set to explore the implementation feasibility and fidelity of a structured newborn responsive parenting intervention program for delivered patients. We will examine their parenting confidence, responsive interactions, and experiences of the intervention, and further compare them with the groups who did not receive the full package intervention.

Rationale for Pakistan and Afghanistan

The Foundations for Health and Empowerment (F4HE) project works in several countries, including Afghanistan, Pakistan, India, the Kyrgyz Republic, and Tajikistan. We decided to conduct this project in two countries, i.e., Pakistan and Afghanistan, with some similar geographical and socio-economic features. This will help us to explore the impact of the intervention in two sites, which can then be replicated on a larger scale.

Research objectives

(1) To explore the impact of early childhood newborn parenting education program intervention on parental confidence, newborn responsive interaction, and parental experiences in the intervention group and further compare these with the cohort without intervention.

(2) To explore the perceptions and experiences of healthcare providers regarding newborn parenting education programs in healthcare settings.

## Materials and methods

Study design

This before-and-after implementation feasibility study will examine the feasibility, fidelity, and adaptation of this intervention in the primary healthcare settings of remote Pakistan and Afghanistan. Implementation research is a relatively new approach in the medical sciences, but it has been widely used in various global, public health, and social sciences research. It also has great potential to allow flexibility for the researchers to be engaged and involved in the process of research. The field sites will be conveniently divided into two groups. The intervention and the control. The intervention group will undergo a structured responsive parenting education program, i.e., six sessions in the first five months of life on a structured curriculum under the supervision of trained lady healthcare workers, while the control group will undergo limited intervention, i.e., a compiled handout at birth for self-study (outlined in Figure 1). 

**Figure 1 FIG1:**
[figure not shown]
Flow chart of the study procedure

Study setting

Participants will be recruited from the six basic health centers (BHCs) of not-for-profit private healthcare systems in Pakistan and Afghanistan. These BHCs will be chosen as primary healthcare facilities to pilot the intervention, as shown in Tables 1-2. The BHCs provide maternal, newborn, and child health services (MNCHS), including antenatal care, delivery, and postnatal care (ANC-PNC), family planning, immunization, adult health screening, and regular growth monitoring of <3 years old. Through lady health visitors (LHVs), responsive parenting education will be integrated into their maternal and newborn care model.

**Table 1 TAB1:** Field sites (Pakistan) F4HE: Foundations for Health and Empowerment

S/n	Site Selection	Location of Health Facility	Type of Health Facility	Level of Services	Average Deliveries Per Month	Covering Under F4HE Geographical Areas
1	Pakistan Intervention Group Site 1 (PIGS 1)	District Upper Chitral	Basic Health Center	Primary	10	Yes
							Pakistan Intervention Group Site 2 (PIGS 2)	District Lower Chitral	Basic Health Center	Primary	4	Yes
	2	Pakistan Control Group Site 1 (PCGS 1)	District Upper Chitral	Basic Health Center	Primary	10							Yes
							Pakistan Control Group Site 2 (PCGS 2)	District Lower Chitral	Basic Health Center	Primary	4	Yes	

**Table 2 TAB2:** Field sites (Afghanistan) F4HE: Foundations for Health and Empowerment

S/n	Site Selection	Location of Health Facility	Type of Health Facility	Level of Services	Average Deliveries per Month	Covering Under F4HE Geographical Areas
							1	Afghanistan Intervention Group Site 1 (AIGS 1)	Baharak District	District Hospital (DH)	Primary and Secondary	265	Yes
							2	Afghanistan Control Group Site 1 (ACGS 1)	Jurm District	Comprehensive Health Center (CHC)	Primary	77	No

Eligibility criteria

Inclusion criteria for the study enrolment are (i) the newborn’s mother following a normal delivery; (ii) the newborn does not exhibit any underlying morbidities; (iii) the family is not living in ultra-poverty with less than 15,000/- total household income; and (iv) the family can understand Urdu. The exclusion criteria for the study include (i) newborns with underlying conditions or morbidities, (ii) the family living on a 15,000 household income per month, and (iii) mothers with postpartum depression.

Study intervention

The Early Childhood (ECD) Newborn Responsive Caregiving Handbook is a pioneering curriculum designed to support parents and caregivers from the newborn stage up to six months of age. Developed through extensive research into caregiver needs and existing knowledge, the handbook addresses the common gaps and uncertainties many caregivers face during the early months of a child’s life. This comprehensive guide consists of six modules covering key topics: breastfeeding, infant cues and behavior, play, maternal postpartum health, neonatal development, and responsive interactions and attachment. Initially drafted with 12 modules, the content was refined to six core areas based on internal and external expert reviews. The finalized curriculum is freely accessible as a downloadable PDF on the Aga Khan University (AKU) website. Participants in the intervention group receive structured teaching sessions over six months, focusing on each module. Additionally, they are provided with take-home materials to reinforce learning. All interventionists undergo training on the curriculum before field implementation. The links to the study intervention content can be found in the Appendix.

Intervention content

The intervention manual consists of six modules around breastfeeding, infant cues and behavior, play, neonatal development, maternal postpartum health, and parent-child interaction. A comprehensive content coverage is provided in Table 3.

**Table 3 TAB3:** Intervention content

Title	Content	Concept
Breastfeeding	Exclusive breastfeeding. Importance of skin-to-skin contact. Breastfeeding positions. Breastfeeding problems. Foods for breastfeeding mothers. Hydration in breastfed babies. Breastfeeding vs. formula feeding	Breastfeeding is the best and complete nutrition during the first six months of a child’s life. Breastfeeding and skin-to-skin contact also improve and promote parent-child interaction and attachment. Breastfeeding-related myths
Infant Cues and Behavior	Definition of infant cues and types of infant cues. Definition of infant behavior. Types of infant behavior, verbal and non-verbal communication with infants	Child’s language. Develop an understanding of the caregiver regarding the child’s needs. Caregiver gives sensitive reactions
Play	Power of play, games to play with infants, age-appropriate toys for infants 0-6 months. Toys and play safely for infants. Low-cost, homemade toys, quick tips for parents	Play makes children learn and explore. Engagement of the caregiver with the child during play
Maternal Postpartum Health	Postpartum maternal health. Postpartum blues, mental health checklist for new moms. Impact of maternal mental health on growing children and asking for help. Postnatal exercises and strategies to support maternal and infant mental health	Mother’s mental and physical health is a priority. It’s ok to ask for help during the postpartum phase. Timely referrals
Neonatal Development	Definition of ECD and nurturing care, domains of ECD. Description of neonatal reflexes and types of neonatal reflexes. Development milestones from 0 to 8 weeks and 3 to 6 months. Strategies for effective newborn care, infant massage, immunization, tummy time, waste disposal, and sleep modulation	ECD and holistic development. Important reflexes and developmental delays. Uniqueness of the child. Routine preventive and hygiene practices
Responsive Interactions and Attachment	Definition of attachment. Introduction to parent-child interaction. Benefits of a father’s engagement. Explaining parent-child interaction with the Barnard model (teaching and feeding interactions). Family bond	Parent-child interaction significance. Teaching interactions. Feeding interactions. Fathers’ engagement

Data collection tools

Basic Demographic Information Form

The basic demographic information form is designed to gather information pertinent to delivery outcomes, caregivers' age, education, socio-economic status, household data such as water and sanitation conditions at home, electricity and technology status, etc. This form also entails caregivers' knowledge about emergency contact numbers and child rights. Additionally, the form gathers some specific information about both the newborn and the mother, such as the mother’s height and weight, and the newborn’s gender and birth weight.

Responsive Interaction Scale

The AKU ECD team has developed a short, responsive interaction scale, which is validated in the local population, that helps practitioners explore the interaction between the caregiver and children from birth to six months. The scale is used to classify newborn handling, responsive interactions, consoling techniques, engagement, and distress. This tool can be used in healthcare and community settings to assess responsive parenting and parent-child interaction.

WHO QoL Scale

This scale is used to assess caregivers' overall well-being and quality of life across multiple dimensions, such as physical health, psychological health, social relationships, and environmental factors.

Karitane Parenting Confidence Scale

This scale helps explore caregivers’ confidence in caring for their infants. It is a self-reported questionnaire, and minimal clinical instructions are required to fill it out.

Harvard CREDI

It helps health professionals to track and assess developmental milestones. The CREDI focuses on measuring children’s early skills and behaviors in four primary domains: motor, cognitive, language, and social-emotional development.

PHQ-9

This self-report questionnaire is used to assess the degree of depression and its severity for screening, diagnosis, monitoring, and providing appropriate help according to their need. It comprises nine self-administered questions for easy evaluation based on the Likert scale.

A Semi-structured Interview Guide

A semi-structured interview guide will be used to explore caregivers’ experiences of the healthcare facility's newborn parenting education programs.

Sample size, recruitment, and enrolment

A total of 500 participants will be chosen, 100 from four primary healthcare facilities in the regions of Chitral, Pakistan, and 100 from two primary healthcare facilities in Afghanistan. A total of 200 before-intervention participants as a control group and 200 intervention participants in Pakistan will be recruited. Similarly, for Afghanistan, 50 pre-intervention (control) participants and 50 intervention participants will be recruited as a control group. The sample size is chosen based on convenience sampling, and the facilities are selected considering the number of deliveries and outreach feasibility. It is anticipated that 40% of the total annual deliveries may consent to participate, and based on calculations, this will help us achieve our N for each of the cohorts. Additionally, there might be variations in the actual data collection.

Data collection plan

We will have two cohorts: a cohort before the intervention and an after-cohort with the intervention. Each cohort will last for six months.

Cohort 1 (control group): Baseline data will be collected, and they will be provided with a self-study pictorial module. They will be tracked and requested to visit the center at six months (child age) post-delivery. At six months, their endline data on responsive interactions, parenting confidence, and patient experience will be collected.

Cohort 2 (intervention group): Baseline data will be collected, and they will be provided a six-month intervention consisting of one session at birth with a self-study manual, and five monthly sessions (once a month till the infant turns six months). At six months, they will also be assessed on the measures mentioned above, and endline will be collected.

Data analysis

Both qualitative and quantitative data analysis strategies will be used to conduct data analysis.

Quantitative analysis will be performed using the statistical package for the social sciences (SPSS Inc., Chicago, IL). Descriptive statistics, such as frequencies, percentages, means, and SD, will be computed for demographic characteristics, QoL, and parental outcomes (confidence, feeding, and teaching assessment using KPSC, NBRI score). Independent sample t-test, paired test, and repeated measure ANOVA will be used to compare within and between-subject effects. Multilevel logistic regression will also be performed for categorical outcomes to observe the effectiveness after controlling for the confounding factors. P≤0.05 will be considered significant.

In qualitative analysis, interviews will be transcribed verbatim and analyzed using software MAXQDA. A coding structure based on the interview guide will be iteratively developed to label specific interview content. The transcripts will be coded, and the two team members will discuss the results and resolve any disagreements in coding by consensus.

Translations, validation, translation, and adaptation of content

In the first round of validation, a group of stakeholders, including healthcare providers, teachers, ECD educators, parents, and grandparents, will be invited to assess the content of the intervention pack. All the relevant feedback will be incorporated into the final version of the curriculum. In the second round, two core groups from the field sites of Chitral and Afghanistan will be invited to explore the potential changes required in the curriculum. In the third round, the curriculum will be sent to the relevant healthcare facilities/community health workers for their rating and feedback. The curriculum was designed in English and will be translated into Urdu and Dari, for which a separate review by two local site co-investigators will be done to ensure its translation validation as per the context. Words that could not be part of literal translation will then be adapted to suit the cultural needs of both regions.

Delivery of the intervention

There will be a structured training whereby internationally trained master trainers in ECD and Keys to Infant Caregiving from Parent-Child Relationship Programs, at Barnard Center, University of Washington and internally certified on ECD PREP ObGyn Aga Khan University curriculum, will provide training to the field site investigators and coordinators, who will then cascade the training to the lady healthcare workers at each study setting. After receiving training, the trained healthcare providers will deliver the content in group-based teaching sessions. Each lady healthcare worker will be selected based on their prior experience in patient and family education by the healthcare facility lead and will undergo a four-day structured training program. Additionally, they will have monthly mentoring check-ins throughout the intervention and will be provided with constant support and random first-hand check-ins by the field coordinators, who will go and co-conduct and observe the session with them. The whole intervention will be closely supervised by the field co-investigators and the lead investigator. An assigned research specialist will conduct monthly meetings to provide the support needed at the field sites.

Ethical considerations

This proposal has received approval from the National Bioethics Commission (No.4-87/NBCR-986/23/323), Pakistan, the Aga Khan University ethical review committee (ERC # 2023-8343-24153), and the Institutional Review Board of Afghanistan (IRB Code No: A-8-24-445). Informed written consent will be sought from all the participants. They will be informed about all the modalities involved in the research project, their rights, and, in no form, will there be names or any identifiable information that will be sought or recorded. All forms will have a unique participant code. All the data will be kept confidential. The data collectors will collect the forms, seal the forms, and send them to the main institution. Additionally, the data will be kept in lock and key. Until the forms are sent here, all the data on the field sites will also remain in a locked drawer.

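### In Afghanistan the arm difference is programme plus facility, inseparably, so it should be reported apart from Chitral and not read as a programme effect

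*Protocol article*

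**What the plan says.** **Afghan sites (Study setting, Table 2).** There is one facility per arm.

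| | Intervention | Control |
|---|---|---|
| District | Baharak | Jurm |
| Type | "District Hospital (DH)" | "Comprehensive Health Center (CHC)" |
| Level of services | "Primary and Secondary" | Primary |
| Deliveries per month | 265 | 77 |
| "Covering Under F4HE Geographical Areas" | Yes | No |

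**Chitral sites (Table 1).** Each arm has one site in Upper and one in Lower Chitral. All four are basic health centers at primary level inside F4HE, with 10 and 4 deliveries a month in each arm.

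**Text.** Study setting describes all six recruiting sites as basic health centers and adds: "These BHCs will be chosen as primary healthcare facilities to pilot the intervention". The sample size section speaks of "100 from two primary healthcare facilities in Afghanistan" and gives the Afghan allocation: "50 pre-intervention (control) participants and 50 intervention participants will be recruited". Pakistan has 200 per arm. The Conclusions, by contrast, refer to both primary and secondary settings.

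**Analysis.** The Data analysis section names independent and paired t-tests and repeated-measures ANOVA. It adds multilevel logistic regression for categorical outcomes, meant to show effectiveness with confounders controlled. No country or site term is named.

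**The concern.** The first research objective is comparative: confidence, responsive interaction and experiences with the programme against those without it. In Afghanistan the two groups differ in the programme and also in type of facility, level of care, district, delivery volume and F4HE coverage. Any of these could plausibly affect how mothers' confidence or interaction scores develop, or which mothers are recruited and return at six months.

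A reader of the text alone would think that like was compared with like, because the prose describes uniform basic or primary facilities and only Table 2 shows otherwise. The limitations section discusses convenience sampling and the instability of the two settings, but not the unlike Afghan facilities. If the listed tests are run on Afghan data, alone or combined with Pakistan, a difference between facilities could be credited to the programme.

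**Working it through.** **1. The plan's own figures.** 200 + 200 + 50 + 50 = 500, which agrees with the stated total. The Afghan numbers are reachable under the article's 40% consent assumption: 265 × 12 × 0.40 = 1,272 and 77 × 12 × 0.40 = 370 a year, against 50 needed at each site. The difficulty is comparability, not recruitment.

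**2. Can arm and facility be separated?** There are two Afghan sites and two arms. A design matrix with columns for intercept, arm and site has rank 2 of 3, because the arm and site columns are identical. Between-site degrees of freedom are 2 − 2 = 0. Enrolling more mothers, adding facility covariates or fitting a site random effect does not change this. The volume ratio is 265/77 = 3.4, and every other tabulated feature differs as well.

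**3. What the baseline can do.** Let the arms differ at baseline by a constant facility amount *a*, and let the facilities also differ by *d* in their six-month change.
- Endline-only difference = programme effect + *a* + *d*.
- Difference in change (or group-by-time term) = programme effect + *d*.

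The planned baseline removes *a* and leaves *d*.

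**4. Size of the bias.** The documents give no value for *d*, so an assumed range of 0.2 to 0.5 SD of the analysed variable is used. In a simple pooled mean difference at planned numbers the Afghan weight is 50/250 = 0.20.

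| Assumed *d* (SD) | Bias in Afghan estimate | Bias if pooled (0.20 × *d*) | Chance that *d* alone gives p ≤ 0.05, 50 vs 50 |
|---|---|---|---|
| 0.2 | 0.2 | 0.04 | 0.17 |
| 0.3 | 0.3 | 0.06 | 0.32 |
| 0.5 | 0.5 | 0.10 | 0.71 |

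The last column uses a standard error of √(2/50) = 0.2 SD and a two-sided 5% level. For example, at 0.5 SD it is Φ(0.5/0.2 − 1.96) = 0.71.

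**5. The same point as a false-positive rate.** Suppose there is no programme effect and the sites vary at random with an assumed intracluster correlation. With one cluster of 50 per arm, the ratio of true to naive variance is 1 + 50·ICC/(1 − ICC). The rejection probability is about 2[1 − Φ(t/√ratio)], where t is the 0.975 quantile on 98 degrees of freedom. For ICC 0.01, 0.02, 0.05 and 0.10 this gives about 0.11, 0.16, 0.30 and 0.44, and simulation agreed.

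**6. Chitral.** The two pairs match on every tabulated feature within district. Each district still has only one facility per arm, so site and arm are aliased within each pair, and two sites per arm leave few between-site degrees of freedom.

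**The case against.** Several points on the other side are fair.

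- **Pooling is not stated.** A reader might infer from the single total of 500 and the undivided list of tests that the Afghan confounding enters the main result. The article never says so. It sets sample sizes by country, and how countries are handled may be left to an analysis plan that is not shown. This stands: the pooled figures are conditional.
- **The baseline helps.** Paired tests and repeated-measures ANOVA are planned, and a constant facility difference cancels there. This stands, but only in part. Differential change remains, and the article does not say whether the independent t-test is on endline or change.
- **It is not a pure facility contrast.** A reader might conclude that the Afghan comparison says nothing about the programme. The table does not support that: the contrast contains both, and they cannot be told apart.
- **A larger Afghan weight.** Applying 40% consent to Chitral's 28 deliveries a month for one year gives 67 per arm, so the Afghan weight would be 50/117 = 43%. This requires assuming a one-year recruitment period that the article does not fix, and it belongs to a separate recruitment question.
- **The design is openly modest.** It is presented as a feasibility study and quasi-experimental, and a randomized trial is recommended later. That lowers expectations but does not disclose the facility imbalance.

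Two other defences do not help. The Abstract says sites are randomly assigned, whereas Study design has them divided by convenience; even true randomisation of two unlike sites would leave arm and facility aliased. Calling controls a pre-intervention group might suggest successive cohorts at one place, but Table 2 fixes separate Afghan sites.

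**Conclusion.** The concern holds in a limited form. With one unlike facility per arm, the Afghan arm difference is programme plus facility, and no analysis of these data can split it. A change-score analysis narrows the problem to differential six-month change but does not remove it. Under an assumed differential shift of 0.2 to 0.5 SD, the Afghan estimate is biased by the full amount; if the countries are pooled at planned numbers, the pooled effect is biased by 0.04 to 0.10 SD. Both the shift and the pooling are assumptions. The aliasing and the misdescription of the sites are read directly from the article.

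The documents do not support saying that the main result will be contaminated, or that Chitral is free of the problem. Chitral is better matched on what is tabulated, but site effects remain there too. Descriptive, feasibility and qualitative use of the Afghan data is unaffected.

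**What to change.** 1. Present the between-arm comparison by country. Base the main comparative statement on the Chitral sites, stating that there are two sites per arm, one per district, so site effects are not excluded.
2. Report Afghan baseline, endline and change by site as feasibility and descriptive results, without attributing the difference to the programme.
3. Correct the description of all six sites as basic health centers (Study setting) and of both Afghan sites as primary facilities (sample size section), so that they agree with Table 2 and the Conclusions.
4. Add the Afghan differences in facility type, level of care, district, volume and F4HE coverage to the limitations.

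No new sites or data are needed; the change is in analysis and wording. The cost is that the comparative claim rests on Pakistan only: 400 of the 500 planned participants, and possibly fewer, since the article's 40% consent assumption gives 28 × 12 × 0.40 = 134 a year from the four Chitral sites.

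### The Urdu requirement for eligibility has no Dari alternative, although a Dari curriculum is planned and 100 of the 500 participants are to come from Afghanistan

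*Protocol article*

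**What the plan says.** Under Study setting, the protocol article says: "Participants will be recruited from the six basic health centers (BHCs) of not-for-profit private healthcare systems in Pakistan and Afghanistan". Tables 1 and 2 list the facilities by country. One set of eligibility criteria follows, not divided by country.

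- **Language.** Inclusion criterion (iv) is "iv) the family can understand Urdu".
- **Income, inclusion.** Criterion (iii) is "the family is not living in ultra-poverty with less than 15,000/- total household income".
- **Income, exclusion.** The second exclusion criterion is "the family living on a 15,000 household income per month".

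The section on translation, validation and adaptation says: "The curriculum was designed in English and will be translated into Urdu and Dari". Co-investigators at the local sites review the translations, and wording that does not translate literally is to be "adapted to suit the cultural needs of both regions". The field sites named there are Chitral and Afghanistan.

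The section on sample size, recruitment and enrolment plans 50 control and 50 intervention participants in Afghanistan.

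**The concern.** An eligibility list defines who may enter, and screeners should be able to apply it in the same way everywhere. Here the list admits only families who understand Urdu, while another section prepares the teaching material in a second language for the second region. The families for whom the Dari version is presumably made are turned away unless they also understand Urdu.

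At stake is the whole Afghan component. The Discussion expects the study to provide evidence for integrating the programme into primary care in Pakistan and Afghanistan. If Afghan enrolment is limited to families who understand Urdu, the results describe that group and need not carry over to other Afghan families. If sites enrol Dari-only families anyway, the sample is closer to the intended one, but each such enrolment departs from the written criteria. These two harms are alternatives: for any given family, one or the other occurs.

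The income wording raises a lesser problem of the same kind. Two screeners reading the two lines could decide differently on the same family.

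**Working it through.** **1. Language rule against translation plan**

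| Family understands | Criterion (iv) | Curriculum version planned |
|---|---|---|
| Urdu only | met | Urdu |
| Urdu and Dari | met | either |
| Dari only | not met | Dari |

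The third row is the contradiction. The article does not state outright that Dari is for the Afghan sites. It follows from the two languages, the two regions and the two site groups named in the same section. No exception by country appears in the eligibility list or elsewhere in the article.

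**2. Share of the study affected**

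Afghan participants: 50 + 50 = 100. Planned total: 400 + 100 = 500. Share: 100/500 = 20%. The language point does not touch the 400 planned in Pakistan.

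**3. Would the rule stop recruitment?**

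Inputs: 265 deliveries per month at the Afghan intervention site and 77 at the control site (Table 2); 40% of annual deliveries expected to consent, and a target of 50 per arm (sample size section).

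Consenting families per year = deliveries per month × 12 × 0.40. Urdu-understanding share needed = 50 / consenting families.

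- Intervention site: 265 × 12 × 0.40 = 1,272; 50/1,272 = 3.9%.
- Control site: 77 × 12 × 0.40 = 369.6; 50/369.6 = 13.5%.

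If recruitment lasted only six months (an assumption), the consenting families halve to 636 and 184.8, and the shares needed double to about 7.9% and 27%.

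The article does not give the actual share. Over one year, assumed shares give:

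| Assumed Urdu-understanding share | Intervention site | Control site |
|---|---|---|
| 50% | 636 | 185 |
| 25% | 318 | 92 |
| 10% | 127 | 37 |
| 5% | 64 | 18 |

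So 50 per arm is reachable within a year over much of this range. A shortfall arises at the control site if the share is below about 13.5%, and at the intervention site only if it is below about 3.9%. This check lets the other criteria exclude nobody, so the shares actually needed are somewhat higher.

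**4. The two income statements**

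| Household income | Inclusion (iii) | Exclusion (ii), read literally |
|---|---|---|
| below 15,000 | fails | not named |
| exactly 15,000 | passes | excluded |
| above 15,000 | passes | not excluded |

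The lines disagree at exactly 15,000. Only the exclusion gives a period (a month), and neither names a currency, although one figure serves two countries.

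**The case against.** The best reply is that this is a drafting slip. A Dari translation, review by local co-investigators and a core group from Afghanistan all suggest that a Dari alternative was intended and left out. That is plausible and makes the correction easy, but the criterion as published still excludes those families.

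A reader might infer several stronger things that the article does not support.

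- **That the Afghan cohorts would be empty.** This needs the Urdu-understanding share, which is not given. The arithmetic above shows that the target can be met with modest shares.
- **That any share below 100% biases the sample.** It restricts the sample. Results are distorted for Afghan families in general only if those who understand Urdu differ on the outcomes. The same rule applies to both Afghan arms, so bias between arms does not follow from it alone. Each Afghan arm is a single facility, so the filter could act differently in the two districts, but nothing in the article shows that it does.
- **That an unrepresentative sample and protocol deviations occur together.** The first follows from obeying the rule, the second from ignoring it.
- **That the income rule selects different strata in the two countries.** This depends on the currency meant, exchange rates and local incomes, none of which is given. A reading in one currency is equally possible.

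It can also be said that the exclusion is a loose restatement of the inclusion, that its period serves both lines, and that a condensed article may leave the currency to the full protocol. This stands in large part and is why the income point is secondary. It does not remove the conflict at exactly 15,000, which is stated in the text.

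The limitations section concedes low generalizability, but attributes it to convenience sampling and does not mention language.

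**Conclusion.** The language criterion and the translation plan contradict each other. As written, Dari-only families are ineligible, and all 100 planned Afghan participants (20% of 500) must come from families who understand Urdu. The consequence is a limit on what can be concluded for Afghanistan or, if sites ignore the rule, enrolments that breach a written criterion.

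Confidence is high on the textual mismatch and low on its effect, which cannot be computed without the Urdu-understanding share. The conclusion rests on one inference, that the Dari version is meant for the Afghan sites. Neither failed recruitment nor a biased comparison of arms is shown.

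The income wording is a minor inconsistency: a conflict at exactly 15,000, a period in one line only, and no currency.

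**What to change.** 1. Change inclusion criterion (iv) to: understands Urdu (Pakistan sites) or Dari (Afghanistan sites).
2. The study is in progress, so record and report which language rule each site has applied so far. Where the Urdu rule was enforced in Afghanistan, describe the Afghan sample as families who understand Urdu. Where it was not, list those enrolments as departures from the published criterion.
3. State the income rule once, with one boundary, the period, and the currency or equivalent used in each country, and delete the second version.

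**Cost.** A short amendment, a corrected screening form and a query to the two Afghan sites. No extra participants or study procedures are needed. The article does not say in which language the questionnaires are given, so the amendment should confirm that Dari-only families can complete them.
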